### Pharmacokinetics

Individual pharmacokinetic analysis will be based on two sets of four blood samples to determine the individual pharmacokinetic profiles of vinorelbine. Sampling times will be calculated by a D-optimality method based on literature data on the pharmacokinetics of vinorelbine [38].

### Circulating biomarkers

During this clinical trial, an ancillary study on biomarker analyses will be conducted: circulating endothelial cells (CEC), fibroblast growth factor 2 (FGF2), vascular endothelial growth factor (VEGF), interleukin-8 (IL-8), and thrombospondin-1 (TSP1) and Tie2/Tek. The results will be analysed to determine any correlation with the data obtained by RECIST in terms of tumour response and/or efficacy.

### Sample size determination and power

The expected number of patients is 32, with the following distribution:Phase Ia: 12 patients will receive VTP: the minimum sufficient number of patients to consolidate the calibration of the model parameters and define the optimal administration schedule (OVTP)Phase Ib: expansion phase after a favourable decision by the monitoring committee.

Twenty patients will receive the OVTP schedule.

The number of patients in the study is based on the Fleming one-step method, with a type I error (α) equal to 5 % and a type II (β) equal to 10 %.

The statistical hypotheses are determined by:p0: disease control rate that would be insufficient to continue with Phase II, set at 25 %;p1: minimum effective control rate to justify the continuation of the phase II trial, set at 50 %.

The following will be tested: H0: *p* = p0 ≤ 25 % versus H1: *p* ≥ p1 = 50 %. According to these hypotheses, the calculation shows that 20 patients should be included in the study.

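### Twenty patients do not give the stated 10% type II error for 25% versus 50% disease control at alpha 5%; exact power is about 75%

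*Protocol article*

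**What the plan says.** Under Sample size determination and power, the protocol article allots 12 patients to phase Ia and 20 to phase Ib, the latter on the OVTP schedule. It names the method, "The number of patients in the study is based on the Fleming one-step method", and the error rates, "with a type I error (α) equal to 5 % and a type II (β) equal to 10" (per cent). The null value is the "disease control rate that would be insufficient to continue with Phase II, set at 25" (per cent). The alternative is the "minimum effective control rate to justify the continuation of the phase II trial, set at 50" (per cent). The test is written out: "The following will be tested: H0: *p* = p0 ≤ 25 % versus H1: *p* ≥ p1 = 50" (per cent). The section ends: "According to these hypotheses, the calculation shows that 20 patients should be included in the study".

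The article gives no cut-off for the number of disease controls and does not say in words whether the test is one-sided, although the hypotheses are written in one direction.

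**The concern.** Every input to the calculation is printed in the section, so the result can be checked without a fuller protocol or an analysis plan. Twenty looked too few for a 25-point difference at these error rates.

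The calculation is the only formal justification for the size of phase Ib, and the two rates are defined by whether the work should go on to phase II. If the true type II error is well above 10%, a schedule that really achieves 50% disease control would miss the 5% criterion far more often than readers are told, and a negative result would be over-read as evidence of inactivity.

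**Working it through.** **Inputs** (all from Sample size determination and power): single-arm, one-step Fleming design; alpha = 0.05; beta = 0.10; p0 = 0.25; p1 = 0.50; stated n = 20. Alpha is taken as one-sided, following the direction of the hypotheses; this is also the reading kinder to the plan.

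**1. Attempt to reproduce 20 with the normal formula**

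n = [z(1−α)·√(p0(1−p0)) + z(1−β)·√(p1(1−p1))]² / (p1 − p0)²

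= [1.645 × √0.1875 + 1.282 × √0.25]² / 0.0625

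= [0.712 + 0.641]² / 0.0625 = 29.3, so 30 patients.

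The stated 20 is not reproduced.

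**2. Exact error rates at n = 20**

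For a rule that rejects H0 when X ≥ r, alpha = P(X ≥ r | n = 20, p = 0.25) and power = P(X ≥ r | n = 20, p = 0.50).

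| Cut-off | Alpha | Power at 50% | Type II error |
|---|---|---|---|
| ≥ 7 of 20 | 21.4% | 94.2% | 5.8% |
| ≥ 8 of 20 | 10.2% | 86.8% | 13.2% |
| ≥ 9 of 20 | 4.1% | 74.8% | 25.2% |
| ≥ 10 of 20 | 1.4% | 58.8% | 41.2% |

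Alpha at or below 5% requires r ≥ 9, where power is at most 74.8%. Power of at least 90% requires r ≤ 7, where alpha is at least 21.4%. The two requirements do not overlap. With the cut-off at 9, power reaches 90% only at a true control rate of 56.7%.

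**3. Smallest exact design for the stated rates**

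Searching upward in n for alpha ≤ 5% and power ≥ 90% gives n = 33 with cut-off 13 (alpha 4.84%, power 91.9%).

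**4. Other readings that might yield 20**

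| Reading | n |
|---|---|
| One-sided 5%, power 90%, variance at p0 only | 25.7 |
| Same, arcsine | 31.2 |
| Same, continuity-corrected | 33.2 |
| Same, variance at p1 only | 34.3 |
| Alpha and beta swapped in value (10% and 5%) | 30.4 |
| One-sided alpha 10%, power 90% | 22.9 (exact 26) |
| Two-sided 5%, power 90%, normal variants | 31.5 to 42.0 (exact 39) |
| One-sided 5%, power 80% | 20.5, rounding up to 21 (exact 26) |

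Of these, only the last comes within two patients of 20, and it uses a beta that the article does not state. On a two-sided 5% reading the cut-off at n = 20 becomes 10 and power falls to 58.8%.

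**5. Pooling both phases**

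With all 32 patients, a cut-off of 13 gives alpha 3.8% and power 89.2%, just short of 90%. But the text attaches the calculation to 20 patients, and the 12 in phase Ia receive VTP, from which OVTP may differ in overall dose or administration schedule (Intervention).

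**The case against.** The arithmetic was not disputed. The case against concerns consequence and remedy.

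- **No binding rule.** The article gives no cut-off, and Statistical analyses says efficacy will be analysed descriptively, with 90% and 95% confidence intervals for the disease control rate. The 25.2% therefore depends on a 9-of-20 rule that the article does not print, and a reader who sees the interval is less likely to over-read a negative result. This tempers the harm. It does not make the stated type II error true: the sample size section says the hypotheses will be tested at 5%, that level fixes the cut-off at 9, and no other cut-off rescues the pair of rates.
- **Endpoint.** Outcomes and assessments makes objective response the primary endpoint of phase Ib, whereas the calculation concerns disease control, a secondary endpoint. That is a fair and separate problem. Any sentence that writes in a disease-control rule should be agreed together with it.
- **Origin of the figure.** The closeness of 20.5 to 20 does not show that 80% power was intended. The formula rounds up to 21, and exact 80% power needs 26. No weight is placed on it here.
- **Early-phase context.** This is a small, non-randomised proof-of-concept trial, and the preferred repair leaves enrolment unchanged. That bears on how much the error costs, not on whether the sentence is right.

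**Conclusion.** The concern holds. The stated design parameters and the stated sample size are incompatible. At 20 patients and a one-sided 5% level, exact power against 50% is 74.8%, not 90%; the type II error is 25.2%, not 10%. A schedule with a true 50% control rate would miss the criterion about one time in four. The stated rates need 33 patients by exact calculation, or 30 by the normal formula.

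This rests on the printed inputs, on a one-sided test (a two-sided one widens the gap), and on the 20 OVTP patients being the analysed set. The practical consequence depends on the phase II decision actually following the test. The misstatement does not depend on that, and it should be corrected before phase Ib is interpreted.

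**What to change.** **Preferred:** keep 20 patients and replace the closing statement of the sample size section, including the 10% type II error, with wording such as:

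*With 20 patients, H0 (disease control rate of 25% or less) is rejected if at least 9 have disease control. The exact one-sided type I error is 4.1%; power is 75% at a true rate of 50% and 90% at a true rate of about 57%.*

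This costs one corrected sentence and a less favourable stated power; recruitment does not change. The sponsor should first settle whether the formal test is on disease control or on objective response, because these figures apply only to the 25% versus 50% disease control hypotheses.

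**Alternative:** if 5% and 10% are to be kept, enrol 33 patients in phase Ib and reject H0 at 13 or more (alpha 4.8%, power 91.9%). That is 13 more patients, a 65% increase (13/20), taking the trial from 32 to 45 and bearing on the planned 12-month inclusion period.

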### Statistical analyses

All patients receiving at least one dose of study drug will be included in the evaluation of safety. All patients who received at least one dose of study drug will be included in the intention-to-treat population and included in the assessment of effectiveness. Patients with valid pharmacokinetic data will be included in the pharmacokinetic analyses.

All efficacy parameters will be analysed descriptively. For the ORR and DCR, estimated 90 % and 95 % confidence intervals will be provided. For the PFS, the duration of the response and overall survival, the Kaplan-Meier method, the median durations and 95 % confidence intervals will be calculated.

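### Phase Ib disease control is to be tested against 25% in one section and only described in the next, and neither of the two planned intervals is tied to the test

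*Protocol article*

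**What the plan says.** In the protocol article, 'Sample size determination and power' sets up a formal decision for phase Ib. It uses a single-stage Fleming design and fixes alpha at 5% and beta at 10%. The null value is the "disease control rate that would be insufficient to continue with Phase II, set at 25" per cent, and the alternative is the "minimum effective control rate to justify the continuation of the phase II trial, set at 50" per cent. The section then announces a test of these hypotheses ("The following will be tested") and arrives at 20 patients.

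'Statistical analyses', which follows directly, states: "All efficacy parameters will be analysed descriptively". For the response rate and the disease control rate, 90% and 95% "confidence intervals will be provided". It mentions no test, no critical count, and no link between either interval and the 25% threshold. The article states neither the sidedness of alpha nor the interval method.

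'Outcomes and assessments' names objective response, not disease control, as the phase Ib primary endpoint.

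**The concern.** A hypothesis that decides whether to go on to phase II cannot be formally tested while every efficacy parameter is only described. The analysis section makes no exception for the test that sized the trial.

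The two interval levels make this matter in practice. A two-sided 90% interval corresponds to a one-sided 5% test, and a two-sided 95% interval to a one-sided 2.5% test. With 20 patients the two can fall on different sides of 25%, and the article does not say which one answers the sizing question. The Discussion expects phase Ia/Ib to provide the rationale for a randomised phase II study, so a borderline result would be read closely.

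**Working it through.** **Inputs.** From 'Sample size determination and power': p0 = 0.25, p1 = 0.50, alpha = 5%, beta = 10%, n = 20. From 'Statistical analyses': 90% and 95% intervals. Assumed, because not stated: alpha is one-sided (the hypotheses are directional and a Fleming design is one-sided), and intervals are exact (Clopper-Pearson). Alternatives to both are shown below.

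**1. The plan's own figure.** Fleming's normal approximation is n = [(z_alpha × √(p0(1−p0)) + z_beta × √(p1(1−p1))) / (p1−p0)]².

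- One-sided 5%, 90% power: [(1.645 × 0.4330 + 1.2816 × 0.5) / 0.25]² = 29.3, so 30 patients. An exact binomial search gives 33 (cut-off 13).
- Two-sided 5%, 90% power: 36 by the approximation, 39 exact (cut-off 16).
- One-sided 5%, 80% power: 20.5, so 21 patients.

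The stated 20 is not reproduced at 90% power; it is close only to the 80% figure. The present point does not depend on this, but any cut-off written into the plan does.

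**2. Critical count with n = 20.** Alpha = P(X ≥ r | 20, 0.25); power = P(X ≥ r | 20, 0.50).

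| Reject at | Alpha | Power |
|---|---|---|
| 8 or more | 10.2% | 86.8% |
| 9 or more | 4.1% | 74.8% |
| 10 or more | 1.4% | 58.8% |

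At one-sided 5% the smallest admissible count is 9. The normal approximation agrees: 20 × 0.25 + 1.645 × √(20 × 0.25 × 0.75) = 8.19, and the next whole number is 9. At two-sided 5% (2.5% in the upper tail) the count is 10.

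**3. Exact intervals around the cut-off.** The lower limit is the Beta(x, n−x+1) quantile at (1−level)/2; the upper limit is the Beta(x+1, n−x) quantile at 1−(1−level)/2.

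| Count | 90% interval | 95% interval | Against 25% |
|---|---|---|---|
| 8/20 | 21.7% to 60.6% | 19.1% to 63.9% | both include |
| 9/20 | 25.9% to 65.3% | 23.1% to 68.5% | 90% excludes, 95% includes |
| 10/20 | 30.2% to 69.8% | 27.2% to 72.8% | both exclude |

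The disagreement falls only on 9/20, the one-sided 5% cut-off.

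**4. Dependence on the interval method.** Lower limits at 9/20:

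| Method | 90% | 95% | Levels disagree about 25%? |
|---|---|---|---|
| Clopper-Pearson | 25.9% | 23.1% | yes |
| Wald | 26.7% | 23.2% | yes |
| Wilson | 28.4% | 25.8% | no |
| Agresti-Coull | 28.4% | 25.8% | no |
| Jeffreys | 28.0% | 25.1% | no |

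At 8/20 and 10/20 the two levels agree under all five methods.

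**5. How often it would matter.** The chance of exactly 9/20 is the difference between adjacent rows in step 2. At a true rate of 50% it is 74.8% − 58.8% = 16.0%; at 25% it is 4.1% − 1.4% = 2.7%. The 16.0 points are also the power lost if the exact 95% interval decides.

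**The case against.** The strongest reply is that the decision rule is already fixed. A Fleming one-step design with stated alpha, p0 and p1 carries its own rejection count, and the intervals only support the estimate. Nothing in the analysis section says that an interval decides. Reporting a 90% interval suits a one-sided 5% test, and adding a 95% interval is ordinary practice. The critical count and interval method are details that an article may leave to the full protocol or analysis plan.

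Much of this stands. Giving two intervals is not an error, and the absence of a stated method or count is not by itself a finding. A reader might infer that the conclusion can be freely chosen once the data are seen. The documents do not support going that far, because method, alpha and both rates are set in advance. A reader might also infer that the two intervals always conflict at the critical count. They do not: three of the five methods tried show no conflict at 9/20, and under two-sided alpha the critical count is 10, where both levels exclude 25%.

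What the reply does not remove is the conflict of wording. One section promises a test; the next makes all efficacy descriptive without exception. That is an inconsistency between two published statements, not a detail left out.

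**Conclusion.** The point holds as a contradiction between the sample-size and analysis sections that should be reconciled. Its numerical consequence is conditional. With one-sided 5% alpha and exact or Wald intervals, the planned 90% and 95% intervals point in different directions at 9/20 and nowhere else near the cut-off. An outcome of 9/20 has a 16.0% chance if true disease control is 50%. Using the exact 95% interval instead of the one-sided 5% test would lower power from 74.8% to 58.8% and alpha from 4.1% to 1.4%. Neither power reaches the 90% implied by the stated beta.

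A reader might also take 9/20 as a success rule for the phase Ib primary endpoint. The documents do not support that: the 25% and 50% are disease control rates, while the primary endpoint is objective response. The vinorelbine response rates cited in the Background run from 7.7% to 18.6%, far below 9/20 = 45%.

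**What to change.** In 'Statistical analyses', replace the blanket statement with wording such as:

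> The disease control rate in phase Ib is tested against 25% with the exact one-sided binomial test at 5%. With 20 patients, H0 is rejected if 9 or more have disease control, which is equivalent to the lower limit of the exact (Clopper-Pearson) 90% confidence interval exceeding 25%. The 95% confidence interval and all other efficacy parameters are descriptive.

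Add that power at this cut-off is about 75% when the true rate is 50%, not 90%, and that the cut-off must be recomputed if the number of patients changes. If two-sided alpha was intended, say so; the count with 20 patients is then 10.

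The wording must name disease control and not refer to the primary endpoint. Which endpoint phase Ib is meant to decide on has to be reconciled separately between 'Outcomes and assessments' and 'Sample size determination and power'. Until then, this wording leaves objective response estimated but not tested.

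The wording change costs a few sentences and no data. Settling the endpoint, or raising the number of patients to reach the stated power, is a larger decision that these sentences do not replace.

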### Monitoring committee

It is expected that a consultation meeting will be organized between the members of the project and the pharmaceutical company Pierre Fabre, after the inclusion of 12 patients in Phase I (4 weeks after the D1 of the 12^th^ included patient). This meeting will aim to analyse the adequacy of the model prediction and clinical outcomes (review of toxicity and clinical efficacy) in perspective with other results held by Pierre Fabre on trials underway elsewhere.

The transition to the second stage will take place after a favourable decision of the monitoring committee.

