### Intervention

Phase IA: patients will be enrolled and treated according to the schedule and the dose defined by the simulated theoretical model VTP. This Protocol (VTP) is based on oral vinorelbine 60 mg on day 1, 30 mg on day 2 and 60 mg on D4, weekly. In this step, data from PD efficacy (tumour assessments and monitoring of biological markers) will be collected and integrated to refine PD model parameters. Possibly, data from other ongoing trials of vinorelbine may be used. The optimal schedule (OVTP) will be simulated by the model. The final schedule will be affirmed after collegial consultation, taking into account biomathematics results, technical requirements and clinical constraints reviewed by oncologists and pharmacologists. From the VTP protocol, the OVTP could have modifications in the overall dose (which should not exceed 10 %) or in the administration schedule.Phase IB: Patients enrolled will receive vinorelbine according to the OVTP protocol obtained in the first step.

Patients will benefit all useful premedications and post-medications.

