### Follow-up and duration of the study

During the continuation of protocol-defined treatment, laboratory tests (cell blood count) and clinical examination will be conducted at D1 of each week. Tumour response will be assessed at baseline and every 6 weeks from the 1^st^ day of treatment by performing a cerebral, thoracic, abdominal and pelvic CT scan. All assessments will be performed by investigators using RECIST version 1.1 (1.1 modified for MPM). The treatment will be administered until radiological disease progression, unacceptable toxicity, or withdrawal of consent.

After the end of the treatment period, patients will be seen every month or contacted by phone to collect data on potential adverse events and survival. The planned duration of the trial is estimated to be 36 months (duration of inclusions: 12 months; Follow-up: up to 24 months after the last patient inclusion).

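### The phase Ia consultation meeting is expected 2 weeks before the 12th patient's first scheduled on-treatment scan, so its efficacy review would lack tumour data for about 1 to 3 of the 12 patients

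*Protocol article*

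**What the plan says.** Four sections of the protocol article bear on this point.

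- **Monitoring committee.** The timing is introduced with "It is expected that a consultation meeting will be organized between the members of the project" and the company, and is placed "after the inclusion of 12 patients in Phase I (4 weeks after the D1 of the" 12th patient. The meeting is to judge how well the model predicted, and to carry out a "review of toxicity and clinical efficacy". The next paragraph adds the gate: "The transition to the second stage will take place after a favourable decision of the monitoring committee".
- **Follow-up and duration of the study.** "Tumour response will be assessed at baseline and every 6 weeks from the" first day of treatment. No earlier on-treatment scan is scheduled. Blood counts are weekly.
- **Intervention.** In phase Ia, "data from PD efficacy (tumour assessments and monitoring of biological markers) will be collected and integrated to refine PD model parameters". The refined model then simulates the OVTP, which all phase Ib patients receive.
- **Sample size determination and power.** The 12 phase Ia patients are described as "the minimum sufficient number of patients to consolidate the calibration of the model parameters and define the optimal administration schedule (OVTP").

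**The concern.** The meeting is asked to look at efficacy and model adequacy at a moment when the latest patients cannot yet have a scheduled response assessment. Both time points are printed in the article, so this is a mismatch between two stated dates and not a detail left to a longer document.

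At stake is the tumour-response part of the calibration. If the efficacy review and the re-simulation use the data available at that meeting, fewer than 12 patients inform the tumour component, although the article presents 12 as the minimum. The schedule given to the 20 phase Ib patients comes out of that step.

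**Working it through.** The plan gives no derived figure to reproduce here. The 4 weeks is a design choice, so the check is a calendar comparison followed by a count of affected patients.

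**Inputs**

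- Meeting: 4 weeks after D1 of the 12th patient (Monitoring committee).
- First scheduled on-treatment CT: 6 weeks after the patient's own D1 (Follow-up and duration of the study).
- Phase Ia size 12, total size 32 (Sample size determination and power).
- Inclusion period 12 months, taken as 52 weeks (Follow-up and duration of the study).
- Accrual at a constant rate: an assumption. The article gives no accrual period for phase Ia alone.

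**Step 1: the gap.** 6 − 4 = 2 weeks. The 12th patient's first scheduled scan falls 2 weeks after the meeting. So does that of any patient whose D1 is less than 2 weeks before the 12th patient's, with a correspondingly shorter delay.

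**Step 2: expected number without a scheduled scan.** This is 1 (the 12th patient) + 2 × r, where r is the accrual rate per week.

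| Accrual assumed | r per week | 2 × r | Expected number of 12 |
|---|---|---|---|
| 32 patients in 52 weeks | 32/52 = 0.615 | 1.23 | 2.2 |
| 12 patients in 3 months (13 weeks) | 12/13 = 0.923 | 1.85 | 2.8 |
| 12 patients in 6 months (26 weeks) | 12/26 = 0.462 | 0.92 | 1.9 |
| 12 patients in 9 months (39 weeks) | 12/39 = 0.308 | 0.62 | 1.6 |
| 12 patients in 12 months (52 weeks) | 12/52 = 0.231 | 0.46 | 1.5 |

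**Step 3: chance that the 12th patient is not alone.** If arrivals are Poisson at the planned overall rate, this is 1 − exp(−1.23) = 0.71. Over the phase Ia range it runs from 0.37 (12 months) to 0.84 (3 months).

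**Step 4: the part that needs no accrual assumption.** The 12th patient always lacks a scheduled scan at week 4. At most 12 − 1 = 11 patients can then contribute scheduled on-treatment tumour data.

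**The case against.** The strongest reply is that the meeting can do most of its work at week 4. The phase Ia primary endpoint is tolerance, judged on grade 3–4 neutropenia, and weekly counts give every patient still on treatment some data. Of the three submodels under Mathematical modelling, pharmacokinetics and haematological toxicity do not depend on CT. For efficacy, the Intervention section also uses biological markers and allows data from other vinorelbine trials. The article nowhere says that all 12 patients need a scan before the meeting. All of this stands, and it limits the point to the tumour-response data of a few patients.

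Three stronger readings are tempting, and the article does not support them.

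- A reader might infer that phase Ib is opened and the OVTP locked on a fixed date at week 4. The timing is only expected. The committee's decision and the collegial consultation that confirms the OVTP have no dates of their own. Equally, no later efficacy cut-off is given, and the meeting is described under the committee's heading just before the transition rule. It is therefore reasonable to read the meeting as informing both steps.
- A reader might infer that the neutropenia proportion is biased low because late patients have short follow-up. The article does not say that the 10 % objective is finally evaluated at this meeting, and an observation window may be left to the full protocol. Cutting every patient at 6 weeks would not remove such a bias.
- A reader might count patients with under 12 weeks on study, or set 28 days against the 160 days simulated in Fig. 1. No section requires two scans, and 160 days is the length of a simulation, not a data requirement.

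**Conclusion.** The mismatch is real and modest. The expected meeting precedes the 12th patient's first scheduled on-treatment CT by 2 weeks. At least 1 of 12 patients, and on average 1.5 to 2.8 depending on how fast phase Ia accrues, would have no scheduled post-baseline tumour assessment when efficacy and model adequacy are reviewed. The minimum of one follows from the stated dates alone, while the averages rest on constant accrual. Patients who started earlier would normally have one scan or more, so the review would not be without efficacy data.

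The consequence for the OVTP is conditional: it arises if the re-simulation uses the data available at this meeting, which the article neither states nor excludes. The case for a change rests on its low cost and on the article's own description of 12 as the minimum for calibration.

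**What to change.** Reconcile the Intervention, Follow-up and Monitoring committee sections. In the Monitoring committee section, set the meeting, or at least the data cut-off for its efficacy review and for the OVTP re-simulation, after the 12th patient's first scheduled 6-week CT has been read, or after that patient has progressed, died or withdrawn if this comes earlier. Any patient who started before the 12th will then have passed the 6-week point too. The early toxicity review can stay at 4 weeks.

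The cost is the 2-week gap plus the time to read the scan, about 2 to 3 weeks in all before phase Ib opens. No scan, visit or other procedure is added.
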